This study is to be conducted in accordance with patient protection principles as outlined in the Declaration of Helsinki, and approved by the appropriate Institutional Review Boards. Each participant will sign the written informed consent before undergoing any examination or study procedure in compliance with Good Clinical Practice. We will utilize a central randomization management system (CRMS) to identify all persons aged 18 to 65 years who meet the diagnostic criteria of CSR and who have a pain score on a Visual Analog Scale (VAS) of more than 4 points and less than 8 points. Patients who initially meet these eligibility criteria will then complete the additional baseline testing (mainly including a VAS, the Borden Index, the Neck Disability Index (NDI) and the 36-item Short Form health survey (SF-36) and will be randomized into either the treatment or the control group.

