### Outcome measurements

The primary outcome is pain severity measured with a Visual Analog Scale (VAS) at baseline, 20 days of the treatment duration and 1- and 3-month follow-up. Secondary outcomes include cervical curvature measured using the Borden method, a composite of functional status measured by the Neck Disability Index (NDI), patient health status (evaluated by the SF-36 health survey) and adverse events (AEs) as reported in the trial.

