### Assessment of patient health status

The SF-36 questionnaire was developed with the aim of measuring CSR patients’ health status. The SF-36 consists of 36 items, 35 of which are used in the calculation of eight separate scale scores. The physical functioning scale (10 items) is the longest scale. The general health and mental health scales have five items each and the vitality and role physical scales have four items each. The role emotional scale has three items and the bodily pain and social functioning scales have two items each. The remaining item of the SF-36 is a health transition question that asks about change in general health over the past 12 months [14]. This questionnaire will be completed at all the measurement points (baseline, the last day of the treatment, 1 and 3 months after the treatment).

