### Statistical analysis

The data will be collected and analyzed according to the intention-to-treat principle. Standard statistical techniques will be used to describe patients’ characteristics in both groups. We will compare baseline characteristics in both groups and, if incomparability appears, we will perform the secondary analysis, adjusting for differences. The primary outcome, VAS, will be compared between both groups using analysis of variance for repeated measures. If adjustment for possible baseline incomparability is needed, analysis of covariance will be done.

All data were analyzed statistically using SAS 9.2 version statistical software. Measurement data were expressed as mean ± standard deviation $$ \left(\tilde{x}\pm s\right) $$, and analyzed using a *t* test; rates were compared using the chi-square test. *P* < 0.05 will be used to indicated that the difference was statistically significant.

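### The continuous secondary outcomes are left by default to an unadjusted t test, with baseline adjustment only if imbalance is seen, so precision available from the collected baseline values is given up

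*Protocol article*

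**What the plan says.** All of the analysis wording is in the Statistical analysis section of the protocol article.

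- **Primary outcome:** "The primary outcome, VAS, will be compared between both groups using analysis of variance for repeated measures".
- **Other continuous data:** summarised as mean and standard deviation "and analyzed using a *t* test; rates were compared using the chi-square test". The sentence names no outcome or visit, and does not say whether the test is on follow-up values or on change from baseline.
- **Baseline comparison, stated before VAS is mentioned:** "if incomparability appears, we will perform the secondary analysis, adjusting for differences".
- **Directly after the VAS sentence:** "If adjustment for possible baseline incomparability is needed, analysis of covariance will be done".

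The outcomes concerned are listed under Outcome measurements: "Secondary outcomes include cervical curvature measured using the Borden method, a composite of functional status measured by the Neck Disability Index (NDI"), followed by the SF-36 and adverse events.

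Their baseline values are available. Under Patients population and recruitment procedure, patients complete "additional baseline testing (mainly including a VAS, the Borden Index, the Neck Disability Index (NDI) and the 36-item Short Form health survey (SF-36") before randomisation. For the SF-36, Assessment of patient health status adds: "This questionnaire will be completed at all the measurement points (baseline, the last day of the treatment, 1 and 3 months after the treatment").

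**The concern.** No method other than the t test is stated for the continuous secondary outcomes, so it is the default for the NDI, the eight SF-36 scales and Borden curvature. Two weaknesses follow.

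1. **Precision.** Patients differ in function, health status and curvature before any treatment. A t test on follow-up values leaves those differences in the error term. Adjusting for baseline removes the part that baseline predicts, and this gain does not depend on the arms being imbalanced. A rule that adjusts only when imbalance is seen gives the gain up in every other case.

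2. **Dependence on the data.** The analysis is settled after the baseline comparison, and the article gives no criterion for incomparability. The general adjustment sentence could cover the secondary outcomes. The ANCOVA sentence follows the VAS sentence and may be meant for VAS alone.

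At stake are wider confidence intervals than the data allow for function, health status and curvature, and a greater chance of missing a real difference. In this one trial, a chance baseline difference too small to be declared would also pass partly into the unadjusted estimate.

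**Working it through.** **The plan's own figure.** The only figure given is the VAS sample size: about 98 per group, 240 in total after 20 % loss. The 98 cannot be re-derived, because the article gives no value for s or δ. With one-sided 5 % and 90 % power it implies δ/s of about 0.418. For the loss to follow-up, 98 / 0.8 = 122.5, or 123 per arm and 246 in total, close to the stated 240. No figure is given for the secondary comparisons.

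**Inputs.**
- Evaluable patients per arm: 240 × 0.8 / 2 = 96, from Sample size considerations and the 1:1 ratio under Randomization and allocation.
- Two-sided 5 % for the power figures (my assumption; the sample size used a one-sided test). The variance ratios do not depend on it.
- Baseline/follow-up correlation r: not in the article; assumed 0.3 to 0.7.
- Equal standard deviation at baseline and follow-up, needed for the change-score formula.

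**Formulas.** Large-sample variance relative to a t test on follow-up values:
- ANCOVA on the outcome's own baseline: 1 − r²
- t test on change from baseline: 2(1 − r)

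| r | ANCOVA variance | Change-score variance | SE reduction, ANCOVA against follow-up t test | Effective n per arm, 96 / (1 − r²) |
|---|---|---|---|---|
| 0.3 | 0.91 | 1.40 | 4.6 % | 105.5 |
| 0.5 | 0.75 | 1.00 | 13.4 % | 128.0 |
| 0.7 | 0.51 | 0.60 | 28.6 % | 188.2 |

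The SE reduction is 1 − √(1 − r²); at r = 0.5, 1 − √0.75 = 0.134.

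**Power.** The SE of the unadjusted difference is √(2/96) = 0.144 SD. The difference detectable with 80 % power is (1.96 + 0.842) × 0.144 = 0.404 SD. For that same difference ANCOVA has power 83.6 %, 89.9 % and 97.5 % at r = 0.3, 0.5 and 0.7.

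**If the t test is on change scores.** ANCOVA is never worse, since 2(1 − r) − (1 − r²) = (1 − r)² ≥ 0. The ratio of ANCOVA to change-score variance is (1 − r²) / [2(1 − r)] = (1 + r)/2, that is 0.65, 0.75 and 0.85 at r = 0.3, 0.5 and 0.7. Compared with the follow-up reading, ANCOVA's advantage is therefore smaller above r = 0.5, the same at 0.5 and larger below it.

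**Chance imbalance.** With 96 per arm, the baseline difference in any one measure has SE 0.144 SD, so its 95 % limits are ±1.96 × 0.144 = ±0.283 SD. A t test on follow-up values carries r times the observed difference. At that limit this is 0.085, 0.141 and 0.198 SD for r = 0.3, 0.5 and 0.7.

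**The case against.** A reader might infer that the plan ignores baseline for every secondary measurement and lets any chance imbalance through. The article does not support that. The general adjustment sentence stands before VAS is mentioned and is not limited to it, so adjustment is conditional, not absent. The t test could also be on change from baseline, which uses the baseline value, though less efficiently than ANCOVA. And that these outcomes are to be compared by t test is itself an inference by elimination, because the sentence is generic.

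It would also go too far to call the secondary comparisons biased or invalid. Under central 1:1 randomisation the unadjusted test is unbiased on average and keeps its type I error. Nor does the article show that the gain would be larger for these outcomes than for VAS. It gives no correlations, and the VAS entry window may also narrow related measures, since the NDI has a pain item and the SF-36 a bodily pain scale.

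Finally, this is a condensed article, and a fuller document may set out a model for each outcome. That would answer a complaint that such models are missing. It does not answer this point, which is about a default the article does state. What stands of the objection is that the point is about efficiency in secondary outcomes for which no power is claimed, and that its size rests on an assumed r.

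**Conclusion.** The point holds in a limited form. The stated default for the NDI, the SF-36 scales and Borden curvature is a t test. Baseline adjustment depends on what is seen at baseline, and its reach to these outcomes is unclear. Precision is given up whenever no imbalance is declared, and the model is not fixed in advance.

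The loss is 5 % to 29 % of the standard error for a t test on follow-up values, if r is 0.3 to 0.7; at the lower end it is small. Under the change-score reading the variances are 0.91 against 1.40, 0.75 against 1.00 and 0.51 against 0.60, so ANCOVA is the better choice either way. The matter is one of efficiency and of chance imbalance in a single trial, not of validity.

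**What to change.** In the Statistical analysis section, replace the t test for the continuous secondary outcomes with a sentence to this effect: the NDI, each SF-36 scale and Borden curvature will be compared between arms by ANCOVA, or by one longitudinal model per outcome over its post-baseline visits, with that outcome's own baseline value as a covariate in every case, whether or not the arms differ at baseline; the adjusted mean difference will be reported with its 95 % confidence interval. State also that the conditional adjustment provision no longer governs these outcomes. If a fuller protocol or analysis plan exists, make the same change there.

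The cost is one degree of freedom per outcome, a simple rule for a missing baseline value, and minor programming in the SAS software already named. No new data, visits or patients are needed. The wording should be settled before outcome data are examined by arm; the article reports that the trial was still recruiting at submission.

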## Discussion

CSR is one of the most common types of cervical disease. The orthopedic of TCM theory holds that both the static system (ligaments, joint capsules, etc.) and the dynamic system (muscles, intervertebral discs, small joints, etc.) are critical in maintaining normal position and function of the cervical spine. The imbalance of both static and dynamic forces can result in a loss of posterior column stability, ultimately leading to rapid degeneration of the cervical intervertebral discs and causing a series of syndromes distributing along the spinal nerve roots (such as pain, numbness of the neck, shoulder and arm, etc.) [17, 18]. Therefore, intervention measurements are aimed at correcting the imbalance between these two systems of the cervical vertebrae and relieving the pain which greatly affects people’s lives and work. For the determination of pain, the self-reported pain method is widely used and a VAS is an accurate method which is recognized internationally [19], hence our use of it for the primary outcome measure.

There is evidence that nonoperative treatment is more effective that operative for treating CSR [4–6], and tuina manipulation is the most common therapy with advantages such as low risk, good therapeutic effect, ease of operation and its economics. It has the effects of dredging meridians, stimulating *qi* and blood circulation, relaxing adhesions and correcting subluxation, ultimately correcting the vicious cycle of the imbalance between the dynamic system and the static cervical vertebral system and establishing the ‘virtuous circle’ instead which is beneficial to the rehabilitation of CSR and thus alleviates clinical symptoms [20–22].

Ears are the converging sites of the meridians and through the connection of meridians, ears are connected to the entire body. It is well-known that stimulating the aural helix can stimulate the corresponding meridians, so that regulating meridian *qi* and blood circulation, thus restoring *yin-yang* balance, will alleviate neck syndromes [23]. In addition, modern medicine shows that stimulating the auricular points can offset or weaken pain through a series of reactions [24]. In this study, BCT incorporates both tuina manipulation and stimulation of the auricular points.

If this study demonstrates the effectiveness and safety of BCT, significant strides would be made towards a clinically useful therapy for alleviating CSR syndrome.

### Trial status

The trial is still recruiting at the time of submission. The first participant was enrolled on 2 August 2016. The trial is expected to complete in August 2017.

## Abbreviations

AEs: Adverse events
BCT: Balance Chiropractic Therapy
CSR: Cervical spondylotic radiculopathy
NDI: Neck Disability Index
TCM: Traditional Chinese medicine
TT: Traction therapy
VAS: Visual Analog Scale
